##### Sleep

Sleep is measured using the Bergen Shift Work Sleep Questionnaire (BSWSQ), which is developed to assess discrete sleep problems related to different work shifts and rest days in shift workers [26]. The questionnaire consists of seven items and is based on the clinical symptoms of insomnia and fatigue/sleepiness, as described in the Diagnostic and Statistical Manual of Mental Disorders (DSM-IV). There is a distinction between insomnia items and fatigue/sleepiness items. The items can be answered on a five-point scale ranging from “never” to “always” for each shift type and for rest days separately. The BSWSQ provides a global score of sleep problems for each shift type. The score concludes insomnia as ‘unfavorable’ when at least one of the insomnia items and at least one of the fatigue/sleepiness items was scored unfavorable. The questionnaire demonstrates good reliability (interclass correlation of 0.69–0.75), and convergent and discriminant validity with other scales [26]. The BSWSQ does not provide information on bed time, sleep latency, wake-up time, amount of hours asleep, sleep medication, and the rating of subjective global sleep quality. These factors are included in the Pittsburgh Sleep Quality Index (PSQI), which assesses sleep disturbances during the past month [24]. Therefore, the BSWSQ is supplemented with the items of the PSQI concerning these factors. The entire PSQI is a widely used measure of sleep quality, with a high reliability of Cronbach’s alpha of 0.80 for the global PSQI score [27]. Also, correlations between PSQI global scores and related constructs exceeds *r* = 0.69, which shows a good construct validity [27].

##### Fatigue

To assess fatigue, the Short Fatigue Questionnaire (SFQ) [25] is used, which is a shortened version of the Checklist Individual Strength (CIS) [28]. The items are “I feel tired”, “I feel physically exhausted”, “I feel fit”, and “I get tired easily”. The questions can be answered on a seven-point scale, ranging from “yes, that is true” to “no, that is not true”. A higher score indicates more fatigue. The Cronbach’s alpha for the SFQ is high, namely 0.72–0.90 [29].

##### Need for recovery

To measure the participants’ need for recovery, the Need for Recovery Scale of the Dutch Questionnaire on the Experience and Evaluation of Work (Dutch abbreviation: VBBA 2.0) is used [30]. The Need for Recovery scale consists of six items concerning the ability to relax, and fatigue and tiredness after work, such as “I find it difficult to relax at the end of a working day”. The items can be answered on a four-point scale ranging from “never” to “always”. The Need for Recovery scale has shown good reliability (*α* = 0.86–0.88), construct validity, and sensitivity to change in The Netherlands [30–32].

#### Secondary outcomes

Secondary outcomes are assessed three times, at the first baseline measurement and at three and six months follow-up.

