#### Study design

A prospective study design is used to investigate the effect of the PerfectFit@Night intervention on sleep, fatigue, and recovery. The intervention is implemented at different hospital departments, making randomization at individual level not possible. Randomization at the work department was not possible, because whether and when the interested departments start PerfectFit@Night is highly dependent on the developments regarding the COVID-19 pandemic. Since randomization at individual level nor work department is possible, the intervention is implemented across at least six departments over a 3 months period, whereby departments move from the control condition to the intervention condition. In this phased pre-post approach within each department there are two periods of data collection before the start of the intervention (1 month and right before the start of the intervention) and two periods of data collection thereafter (3 months and 6 months after the start of the intervention).

The study has been approved by the Medical Ethical Review Committee of the Erasmus University Medical Center (Erasmus MC) and registered in the Netherlands Trial Register under trial number NL9224.

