### Study population

The study population consists of all healthcare workers working night shifts from at least six different departments of the Erasmus University Medical Center in the Netherlands. The participants that completed the baseline questionnaires were asked to fill out a short questionnaire before the start of the intervention period, and follow-up questionnaires after three and six months after the start of the intervention (i.e., a total of four measurements).

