### Sample size

A power calculation was conducted to determine the sample size. The calculation is based on the number of night workers needed to identify a medium effect-size (at least 0.27) in sleep quality, as measured with the Bergen Shift Work Sleep Questionnaire (BSWSQ) [26]. A previous study among nurses working night shifts reported a mean sleep quality of 1.75 with a standard deviation (SD) of 1.26 [26]. The design of the study is a before-after study with four measurements (two before and two after the intervention period). Assuming equal within- and between-person variance with an ICC of 0.05 for clustering at the department level, and an average cluster size of 20, five departments should be included to obtain a power of 0.80 at a significance level of 0.05. This means 100 participants should be included in total. Taking into account an initial participation of 70% and a loss-to-follow-up of 30%, the number of night workers needed at baseline is 204. It could be in practice that cluster sizes are larger than described in this power calculation. This will not have any consequences as we applied the most conservative sample size within this prospective study design with repeated measurements.

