#### Primary outcomes

The primary outcome measures are sleep, fatigue, and need for recovery, which are measured at all four time points.

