##### Sleep hygiene

Six self-constructed questions are asked regarding sleep hygiene, e.g. about taking naps during nights shifts, and taking into account what to eat and drink during and after night shifts. The items can be answered on a four-point scale ranging from “never” to “always”.

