##### Sustainable employability

Sustainable employability is measured using three items of the Work Ability Index (WAI) [33]. The sub-items of the WAI can be used as a simple indicator for assessing the status and progress of work ability. Therefore, the first item of the WAI is included, which asks the question “Assume that your work ability at its best has a value of 10 points. How many points would you give your current work ability?” that can be answered on a scale ranging from 0 to 10. Additionally, two items on the own rating of work ability related to physical and psychological job demands are asked. These items can be answered on a five-point scale ranging from “very good” to “very bad”.

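### Secondary outcomes are left off the pre-start questionnaire that the same workers already complete; adding the short items would be a cheap gain in precision and in before-start evidence

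*Protocol article*

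**What the plan says.** The Study design section explains that neither workers nor departments could be randomised. Departments start in phases, "whereby departments move from the control condition to the intervention condition". Within any one department the plan is that "there are two periods of data collection before the start of the intervention (1 month and right before the start of the intervention"), followed by collections at 3 and 6 months.

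The outcome sections treat the two classes of outcome differently:

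- **Primary outcomes** (sleep, fatigue, need for recovery), "which are measured at all four time points".
- **Secondary outcomes** (sleep hygiene, sustainable employability, dietary intake, general health): "Secondary outcomes are assessed three times, at the first baseline measurement and at three and six months follow-up".

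The omitted occasion is not a missing contact. Under Study population, participants who completed the baseline questionnaire "were asked to fill out a short questionnaire before the start of the intervention period".

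Some secondary measures are very short. General health is one RAND-36 item. Sustainable employability is three Work Ability Index (WAI) items, of which the first is a 0–10 rating, and the protocol says of them: "The sub-items of the WAI can be used as a simple indicator for assessing the status and progress of work ability". On sleep hygiene: "Six self-constructed questions are asked regarding sleep hygiene, e.g. about taking naps during nights shifts".

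The Effect evaluation section gives one set of mixed models for all outcomes and does not separate those with two pre-measurements from those with one.

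**The concern.** With no randomised or parallel control, the information on what happens without the intervention comes from the time before each department starts. Two pre-measurements show at least a short stretch of unexposed change in the same people. One pre-measurement shows none. For the secondary outcomes, any shift between month −1 and the start, whether from answering the questionnaire a second time or from short-term drift, is counted in the before-after effect.

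An analysis plan cannot repair this later, because an occasion that was not collected cannot be modelled back in. The outcomes also matter to the programme. The Abstract and Background present sustainable employability as something the intervention should contribute to, and taking powernaps is one of the five programme objectives in Methods. Start dates depend on the COVID-19 pandemic (Study design; Strengths and limitations), so changes over time in hospital staff are a realistic worry.

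**Working it through.** **Inputs from the protocol**

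- Occasions: primary 2 before and 2 after; secondary 1 before and 2 after (Primary outcomes; Secondary outcomes).
- Variance structure (Sample size): "Assuming equal within- and between-person variance with an ICC of 0.05 for clustering at the department level, and an average cluster size of 20". With total variance 1, the within-person variance is σ²w = 0.5.
- Effect size 0.27, power 0.80, significance level 0.05, five departments, 100 participants; 70% participation, 30% loss, 204 at baseline (Sample size).
- Assumed here: 0.27 is a standardised effect, and the test is two-sided.

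**Step 1. Reproduce the plan's own figure**

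Variance of the before-after change = σ²w (1/pre + 1/post) × DE / N, with design effect DE = 1 + 19 × 0.05 = 1.95.

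- Two before, two after, N = 100: variance = 0.5 × 1 × 1.95/100 = 0.00975, SE = 0.0987.
- Power = Φ(0.27/0.0987 − 1.96) = 0.78, against 0.80 stated. For exactly 80%, N = 105.
- Inflation: 100/(0.7 × 0.7) = 204.

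The protocol's numbers are therefore closely matched by a pooled before-after contrast with two measurements on each side.

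**Step 2. Remove one pre-measurement**

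- Two before, two after: σ²w (1/2 + 1/2) = σ²w.
- One before, two after: σ²w (1 + 1/2) = 1.5 σ²w.
- SE ratio = √1.5 = 1.225, or 22% larger. In the other direction, adding the second pre-measurement cuts the SE by 1 − 1/1.225 = 18%.

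Generalised least squares with six departments of 20 (person and residual variance 0.475 each, department variance 0.05) agrees: √(0.475/120) = 0.0629 and √(0.475 × 1.5/120) = 0.0771, ratio 1.225.

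For illustration only, since the protocol gives no effect size or SD for a secondary outcome: at effect 0.27, N = 100 and DE 1.95, power is 0.61 with one pre-measurement and 0.78 with two.

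**Step 3. How far the 22% depends on the model**

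The variance components beyond the protocol's, the correlations and the start dates below are assumptions.

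| Model | SE penalty |
|---|---|
| Pooled contrast, independent within-person errors | 22% |
| 3-month contrast only | 15% |
| Linear calendar trend | 15% |
| Intervention effect varying by department (variance 0.05) | 8% |
| Three-month calendar periods, by start dates and variance structure | 9–45% |
| Serial correlation 0.3 / 0.5 / 0.7 per month, occasions at −1, −0.25, 3 and 6 months | 12% / 9% / 7% |

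**Step 4. What phased starts can add**

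Suppose starts are spread over months 0 to 3. First baselines then fall in months −1 to 2, and post-measurements begin at month 3. No unexposed secondary value coincides in time with an exposed one, and with separate monthly calendar effects the three-occasion effect is not identified. With four occasions it is identified, but only narrowly, through departments that start about 3 months after the first. If all starts fall within two months, neither schedule identifies it.

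**The case against.** The strongest reply is that this is a deliberate and openly stated trade-off. The evaluation is aimed at sleep, fatigue and recovery, which keep both pre-measurements. Shortening a form sent a few weeks after the first is reasonable when 30% loss is expected. No power or precision is claimed for the secondary outcomes, so no stated figure is wrong. That stands: a reader might infer a contradiction or an error from the differing schedules, but the protocol states them consistently.

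Three other strong readings are also tempting and not supported:

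- *Nothing in the data could reveal drift or retest effects.* The same workers give two pre-measurements of the primary outcomes, the Process evaluation collects data on use of the powernap bed, and phased starts give unexposed levels from different departments at different dates. This evidence is indirect or between departments, and Step 4 shows how weak the last part can be, but it exists.
- *The 22% is a general loss.* It needs independent errors and a pooled contrast, and the equal-variance assumption was made for sleep quality. Serial correlation over a gap of about 3–4 weeks is plausible, and the past-month recall windows for diet partly overlap.
- *Napping is the programme's chief target.* Methods lists five objectives without ranking them.

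The second pre-measurement also has limits of its own. It cannot show trends over 3–6 months. If announcing the programme raises expectations, a measurement in the week before the start may already contain that effect, and averaging it into the baseline does not remove it.

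What remains is that the contact already exists, some of the omitted measures are very short, and the lost occasion cannot be recovered in the analysis.

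**Conclusion.** The point holds as a cheap improvement. For the secondary outcomes no unexposed change can be observed within a person or department, and short-term effects between month −1 and the start are merged with the before-after effect. The precision cost is 22% in the standard error under the structure that closely matches the protocol's own sample size (independent within-person errors, pooled contrast). It is about 7–12% under the assumed serial correlations and roughly 8–45% under the other mixed models tried. Because these are secondary outcomes and the limits of a 3–4 week gap are real, the consequence is moderate. It does not touch the primary analysis.

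**What to change.** 1. Add the short secondary items to the pre-start questionnaire: the WAI current work ability rating (0–10), preferably with the two other WAI items so that the whole employability measure is repeated; the RAND-36 general health item; and the sleep-hygiene question or questions on taking naps. The protocol does not say how many of the six concern naps.
2. Include both pre-measurements in the mixed model, and report the change between them beside the before-after effect.
3. For outcomes left with one pre-measurement (dietary intake, the remaining sleep-hygiene items), describe the before-after change as uncontrolled.

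The cost is a handful of items on an existing form, with a slight increase in burden and no new contact. The gain is limited to precision and short-term change before the start. The Data Availability statement says that no quantitative data had been collected, while Study population describes the questionnaires in the past tense. If the pre-start form can no longer be changed, item 3 should apply to all secondary outcomes.

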##### Sleep hygiene

Six self-constructed questions are asked regarding sleep hygiene, e.g. about taking naps during nights shifts, and taking into account what to eat and drink during and after night shifts. The items can be answered on a four-point scale ranging from “never” to “always”.

##### Sustainable employability

Sustainable employability is measured using three items of the Work Ability Index (WAI) [33]. The sub-items of the WAI can be used as a simple indicator for assessing the status and progress of work ability. Therefore, the first item of the WAI is included, which asks the question “Assume that your work ability at its best has a value of 10 points. How many points would you give your current work ability?” that can be answered on a scale ranging from 0 to 10. Additionally, two items on the own rating of work ability related to physical and psychological job demands are asked. These items can be answered on a five-point scale ranging from “very good” to “very bad”.

##### Dietary intake

Assessment of the dietary intake is focused on the consumption of beverages and snacks during night shifts generally over the past month. Participants are asked to indicate the amount of water, caffeinated coffee, caffeinated tea, and energy drinks they consumed, and whether they ate pre-specified snacks. The snacks are categorized, based on the revised version of the Fat List [34]. For each type of snack, it is asked whether this was eaten “never”, “sometimes”, “often” or “always”.

##### General health status

is measured subjectively using a single item of the RAND-36 Health Survey on self-perceived health status [35]. The answer options range from “very good” to “very bad”.

#### Covariates

A number of covariates are measured once at baseline.

##### Individual characteristics

Demographic characteristics such as age, gender, and household composition are collected, as well as work factors such as job title, number of years in night work, frequency of night shifts, and working hours.

##### Chronotype

To assess whether de participants are morning, evening, or intermediate type persons, the night workers are asked whether they consider themselves “definitely a morning person”, “more a morning than evening person”, “more an evening than morning person”, or “definitely an evening person”. A single question regarding self-reported chronotype has shown to be in excellent agreement with chronotype assessment based on sleep times [36].

##### Body mass index (BMI)

The participants are asked to state their height and weight. BMI will be calculated by dividing weight (in kilograms) by the square of height (in meters).

##### Physical activity

Physical activity is assessed by two questions regarding the amount of days a week an individual spends more than 30 moderate and high intensity active minutes in leisure time in general.

##### Psychological job demands

Three items of the Job Content Questionnaire (JCQ) are used to assess psychological job demands. The items measure how fast, much, and hard an individual’s work is [37]. The questions can be answered on a five-point scale ranging from “never” to “always”. The Cronbach’s alpha for the psychological job demands scale is 0.63, which indicates an acceptable reliability [37].

##### Job autonomy

Another five items of the JCQ are used to assess autonomy at work [37]. These items concern decision making, deciding on the order and speed of conducting tasks, having to find solutions, and being able to take time off. The five items are supplemented with two items on the influence on work rosters, and the opportunity to take breaks. The questions can be answered on a five-point scale ranging from “never” to “always”.

##### Social support at work

To assess social support at work, four items of the Copenhagen Psychosocial Questionnaire (COPSOQ) are used [38]. The items concern questions about help and support from colleagues and supervisors, and about how often colleagues and supervisors are willing to listen to work-related problems. The items can be answered on a five-point scale ranging from “never” to “always”. The four items have a test-retest reliability of 0.70–0.73, indicating an adequate reliability [39].

##### Emotional strain

Three items of the COPSOQ are used to assess emotional strain of the job [38]. These items concern emotionally difficult situations, emotional demands, and emotional involvement with work.

##### Rewards

Another three items of the COPSOQ are used to assess appreciation, recognition, and respect of the management, as well as fair treatment at work [38]. The items can be answered on a five-point scale ranging from “to a very small extent” to “to a very large extent”.

##### Rosters

Five self-constructed items are used to get insight in the rosters of the night workers and how satisfied they are with the rostering process. Three items concern the roster process (e.g., whether the rosters are known in a timely manner), which can be answered on a four-point scale ranging from “never” to “always”. Two items concern the questions whether complaints about the rosters are taken seriously, and whether the night worker wants to have more say in the rosters. These two items can be answered with “yes”, “no”, or “not applicable”.

##### Department characteristics

To be able to test for differences in outcomes between departments, information on the department the employee works at and the amount of night workers at that department are collected.

### Effect evaluation

Baseline characteristics of the participants and of the departments will be summarized using descriptive statistics to detect possible selection bias and lack of balance between departments. To evaluate the effectiveness of the intervention, linear mixed effects models will be applied for scale-scores, and generalized linear mixed models for dichotomous outcomes. These statistical methods take into account the repeated measures of the study design. The analyses will be adjusted for important confounders based on the individual participants and the department, and both statistical tests and confidence intervals will be calculated (with a significance level of 5%). The difference in starting point across the departments and the multilevel structure of the departments will be taken into account. In order to analyze whether the (in)effectiveness of the intervention is moderated by the implementation factors, the linear and generalized mixed models will be expanded with the process factors that emerge from the process evaluation to evaluate whether higher uptake and quality of implementation is associated with higher effect size.

### Process evaluation

The implementation process will be evaluated after the intervention period by assessing the seven components of the framework of Steckler and Linnan [40]. These are 1) recruitment: description of the procedures used to approach and attract hospital workers with night shifts to take part in the intervention; 2) reach: the proportion of hospital workers with night shifts that actually participated in one of the intervention elements; 3) dose delivered: the delivery of all intervention elements as described in the protocol; 4) dose received (compliance): the proportion of night workers that received all intervention elements; 5) fidelity: the extent to which the intervention is implemented following the intervention protocol and the implementation plan; 6) satisfaction: satisfaction of the night workers and other stakeholders about the PerfectFit@Night intervention; 7) context: the barriers and facilitators that might hamper or enhance implementation. Both quantitative and qualitative data will be collected. Quantitative data can be, for example, records of the participation in the workshop, the amount of participants that started and completed the e-learning, usage of the powernap bed and sleep coaching, and reports from the questionnaire about satisfaction with the intervention elements. Qualitative data will be collected via interviews with night workers and focus groups. Interviews will be conducted with at least two night workers from each participating department, and other stakeholders (i.e., managers, human resources) 3 months after enrolment in the intervention. The interviews will be one-on-one following a semi-structured protocol, and they will be audiotaped and transcribed. To identify common themes, two project members will analyze the first four transcripts separately. This ensures both consistent and robust coding following the process evaluation framework. Qualitative, open-ended questions from the questionnaires will be coded manually in the same manner as the interviews, and logbook data will be grouped per department to form a chronological list of events. Additionally, two focus group discussions with four team managers of different departments will be organized.

Reach, dose received, and dose delivered will be assessed based on descriptive statistics of the quantitative data. Questionnaires, interviews, and logbooks will be used to study fidelity, satisfaction, and context.

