### Intervention elements

Based on the needs assessment and program objectives, the intervention consists of the following individual and environmental elements (see Fig. 1): i) an e-learning for night workers to increase knowledge and awareness on a healthy lifestyle during night shifts, ii) a powernap bed to take powernaps during night shifts, iii) the availability of healthy food/snacks at the department during night shifts, iv) a workshop on healthy rostering at the level of the department (for roster makers), and v) individual sleep coaching among the high risk group.

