#### Workshop on healthy rostering

Having insight in healthy rostering at the level of the department is targeted by a workshop that focuses mainly on staff members, team leaders, and managers dealing with the rosters. The workshop will be tailored to the department. Even though research shows that forward rotating rosters have the best effects, the optimal roster for shift workers remains unknown. The workshop aims to motivate roster makers to have conversations with their workers about the rosters. In line with the ANGELO-framework, the workshop aims to start a conversation at the workplace about changing the rosters (i.e., political factor), and motivate to actually make changes to the rosters (i.e., physical factor). Also important is the acceptance from the management and the workers that the rosters change (i.e., socio-cultural factor), and a sufficient amount of workers to change the rosters (i.e., financial factor). The social context with financial and human resources consequences will also be addressed.

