#### Coaching among risk group with existing large sleep problems

The previously described intervention elements are mainly focused on universal prevention of risks due to night work. Additionally, night workers with existing large sleep problems and fatigue are offered sessions with a sleep coach to reduce these problems (indicated prevention). Night workers that score low on subjective global sleep quality (assessed using Pittsburgh Sleep Quality Index (PSQI) [24]) and high on fatigue (assessed using the Short Fatigue Questionnaire (SFQ) [25]) at the baseline measurement are offered coaching sessions, online or face-to-face. The coaches provide evidence-based methods, based on cognitive behavioral therapy insomnia (CGTi), to target the individual problems of the night workers. Participants who accept the invitation for coaching sessions are offered 2–3 sessions of 30–40 min, based on the needs of the individual. During these sessions, the coach proposes the relevant topics to be discussed based on the individual needs and issues of the participant. Before the first session, participants are asked to fill out a screening form, a questionnaire regarding cognitions about sleep, and an online sleep journal for 2 weeks. During the first session, the trajectory and goals are discussed and specified. Then, the participants’ biological rhythm is discussed, specifically taking into account the irregular work shifts. Targeted information and tips about the irregular rhythm and sleep in general are also given by the coach. During the second session, the previous exercises are discussed. Thereafter, practical tips regarding lifestyle, sleeping behavior, and relaxation are given. It is also evaluated whether a third session is needed. During the third session, exercises that need follow-up are discussed, as well as applications of the techniques in the future.

The intervention will be implemented throughout a period of 3 months, and thereafter may continue at the discretion of participating individuals and departments within the hospital.

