### Strengths and limitations

The first strength of this intervention is its integrative character. The intervention is a combination of universal prevention and indicated prevention, and it targets both individuals and the work environment. Second, the evaluation of both effectiveness and implementation makes it possible to distinguish between theory and program failure.

The study also has some limitations. First, the integrated nature of the intervention makes it impossible to make conclusions about the effects of each individual intervention element. Second, it depends on the willingness of the department heads to invest in the powernap beds and healthy nutrition. Third, whether and when the interested departments start the PerfectFit@Night is highly dependent on the developments regarding the COVID-19 pandemic, making randomization at the individual and work department not possible. Last, the time frame of the intervention leads to the inability to draw conclusions on the long-term effects.

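### Dose received requires all five elements, two of which are not offered to every night worker, so compliance is capped below 100% even with perfect delivery

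*Protocol article*

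**What the plan says.** The Process evaluation section of the protocol article lists seven components. The fourth is "dose received (compliance): the proportion of night workers that received all intervention elements". The denominator is night workers and the numerator requires every element. Reach, the second component, is separate: it asks only for participation in one element.

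The Intervention elements section lists five elements. E-learning, the powernap bed and healthy food are for all night workers. The last two are "a workshop on healthy rostering at the level of the department (for roster makers), and v) individual sleep coaching among the high risk group". The workshop section describes "a workshop that focuses mainly on staff members, team leaders, and managers dealing with the rosters". The coaching section limits the offer to night workers who score low on PSQI sleep quality and high on SFQ fatigue at baseline, and participation is by acceptance of an invitation.

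The Effect evaluation section adds process factors to the mixed models "to evaluate whether higher uptake and quality of implementation is associated with higher effect size", without naming the factors. Strengths and limitations states that "the evaluation of both effectiveness and implementation makes it possible to distinguish between theory and program failure".

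**The concern.** The definition conflicts with the intervention it is meant to measure. A worker without marked sleep problems is never offered coaching, so cannot receive all elements however well the programme runs. Read as a compliance rate, the result would understate uptake by an amount set by eligibility and not by behaviour or delivery.

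There is a second consequence. Only workers with poor sleep and high fatigue at baseline could count as compliant, and sleep and fatigue are primary outcome domains. If this indicator were used as a moderator, compliant and non-compliant workers would differ in baseline severity by construction. A larger improvement among compliant workers could then reflect regression to the mean as much as uptake.

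**Working it through.** The article states no expected value for dose received, so there is no figure to reproduce. The check is the highest value the definition can reach when every worker takes up everything offered.

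**Inputs**
- Five elements, all required: Intervention elements and Process evaluation sections.
- p_c, the share of night workers offered coaching: not stated, and no PSQI or SFQ cut-off is given. Assumed 10–50%.
- p_r, the share of night workers who make rosters: not stated. Assumed 2–20%.
- Uptake of every offered element: set to 100%, to obtain the ceiling.

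**Reading A: the workshop is credited to every worker in the department.** Only coaching restricts receipt.
- Ceiling = p_c, that is 10% to 50%.
- Coaching is voluntary, so the attainable value is p_c × acceptance. With 30% offered and 50% accepting (both assumed): 0.30 × 0.50 = 15%.

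**Reading B: the workshop is counted per person.** A worker must be both a roster maker and offered coaching.
- Under independence, ceiling = p_r × p_c. Lowest: 0.02 × 0.10 = 0.2%. Highest: 0.20 × 0.50 = 10%.
- With maximum overlap, ceiling = min(p_r, p_c). Lowest: min(0.02, 0.10) = 2%. Highest: min(0.20, 0.50) = 20%.

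**Example with 100 night workers, 30 offered coaching and 5 making rosters (assumed), all taking up everything offered**

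| Counting rule | Workers counted as compliant |
|---|---|
| Reading A | 30 |
| Reading B, independence | 0.05 × 0.30 × 100 = 1.5 |
| Reading B, maximum overlap | 5 |
| Every element the worker was offered | 100 |

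On either reading, a worker not offered coaching can never count. Once each element is assessed among those to whom it was offered, the ceiling is 100% again.

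**The case against.** The strongest reply concerns the workshop. The article places it at department level, says it focuses mainly (not only) on those dealing with rosters, and describes its effect as running through changed department rosters. The coaching section also groups it with the elements mainly aimed at universal prevention. It can therefore reasonably be credited to every worker in the department. On the other side, the workshop is labelled as being for roster makers, and the process data include workshop participation records. Both readings are open, so a reader who infers that compliance must be near zero goes too far. That needs the per-person reading and assumed shares; on the department reading the ceiling could be as high as 50% within the assumed range.

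Two further inferences are tempting and not supported:
- *That this indicator will enter the moderation models.* The Effect evaluation section refers only to factors that emerge from the process evaluation. The Process evaluation section assigns dose received to descriptive statistics. Its use as a moderator is possible but not stated.
- *That theory failure and programme failure can no longer be told apart.* Six other components remain, including reach, dose delivered, fidelity and context, supported by interviews, focus groups and logbooks. One misleading descriptive figure does not cancel these.

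It can also be said that a condensed article leaves operational definitions to the full protocol, and that the listed element-level records would allow a better measure. The second part is true and makes the repair cheap. The first does not remove the problem: the article does not leave the definition open but states a rule that conflicts with its own account of who is offered what.

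**Conclusion.** The point holds as a minor correction. As defined, dose received cannot reach 100% unless every night worker qualifies for coaching, because workers who take up everything offered to them are counted as non-compliant. This follows from the text alone. The size does not: with 10–50% offered coaching and 2–20% roster makers, both assumed, the ceiling is 10–50% if the workshop is credited to the department. If the workshop is counted per person, it is 0.2–10% under independence or at most 2–20% with maximum overlap. Incomplete uptake lowers all of these.

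The mixing of uptake with baseline severity is conditional: it arises only if this indicator is chosen among the process factors in the outcome models. The primary effect estimates, sample size, power and significance level do not depend on the definition.

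**What to change.** Replace the all-elements definition as follows:
- Report dose received separately for each element, among the workers to whom that element was offered: e-learning, powernap and food for all night workers; coaching among those invited.
- Report the rostering workshop at department level, and state how it is credited.
- If uptake is used as a moderator, base it on the three universally offered elements. Examine coaching uptake separately, among those offered coaching only. A single score over all the elements a worker was eligible for is less suitable as a moderator, because its denominator would still depend on baseline sleep and fatigue.

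The cost is a change of wording and slightly more reporting. Records of workshop participation, e-learning, bed use and coaching are already among the example data sources. Use of the food provided is not listed there, so it would need a usage record or a questionnaire item.
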